### Timeline

This study will last 17 months. The first 5 months will be the baseline survey. Given the total population of MSM are small in some cities, we wanted to ensure sufficient time for participant recruitment. CDC surveillance surveys will also be conducted in participating cities. The following 12 months will be the intervention phase. The intervention will be implemented in City F, City G, City H, City I, City J, and City K following the cluster RCT design outlined in Fig.2. All the participants in the eleven cities will be surveyed at baseline and every 3 months thereafter. In the 17th month, the last follow-up survey will be implemented.

### Data collection and management

The Sojump Survey Software will be used for data collection and storage. In this study, we will collect information about socio-demographics, sexual behaviors, HIV and syphilis testing behaviors, social network characteristics, and psychological characteristics through an online questionnaire. The online tool and questionnaire were used in our original stepped wedge cluster randomized controlled trial [29]. Socio-demographic characteristics include age, occupation, education level, annual income, marital status, sexual orientation, and sexual orientation disclosure. Behavioral variables consist of sex partners, frequency of sex, condom use, self-reported HIV testing (including both facility-based and self-testing), syphilis testing, and social networking. Psychological characteristics include HIV testing self-efficacy and HIV stigma.

To improve data quality, we have set up a verification mechanism. When a questionnaire has been completed, we will check it first. If it has only one logical error, we will verify with the participant. When there is more than one logical error in the questionnaire, the participant will no longer be included in the study. All questions in our online survey have been set as compulsory questions, which can improve data completeness.

Final survey data completed by all participants will be saved in a secure computer only used for saving data, discarding other privacy issues such as open network environments. Passwords and firewalls will also be used to protect the data.

An internal advisory committee composed of STI experts has been established. The committee will guide us in study design and data analysis and meet regularly to review and assess progress in data collection and research.

### Analysis

The socio-demographic characteristics will be analyzed using descriptive statistics. Comparison in baseline characteristics between the intervention and control arm will be conducted using a chi-squared test adjusted for clustering. The primary outcome of this trial will be the uptake of self-reported HIV testing rate after 12 months. Generalized linear mixed models (GLMM) will be used for the analysis. Intervention status and time will be considered fixed effects, while sites and individual participants with multiple measurements across the four follow-ups will be considered random effects.

The secondary outcomes will include a series of binary variables (continuous variables will be categorized into binary variables), such as number of sexual partners, frequency of anal sex, sex without condoms, frequency of HIV testing (including both facility-based and self-testing), awareness of syphilis status, social network engagement, and others. These will be analyzed similar with the primary outcomes. Furthermore, the interaction effect of intervention between individual level and community level will also be analyzed.

After the 2nd follow-up, we will conduct an interim analysis to evaluate the effectiveness of digital images and videos. After the 4th follow-up, we will also evaluate the effectiveness of digital media and self-test kit using data collected from the 3rd and 4th follow-ups.

The data cleaning, sorting, and analysis will be carried out by team members who do not participate in the randomization and city administration and do not know the treatment allocation. Data analysts were not allowed to modify or delete data. If an outcome is missing for < 15% of participants, analyses will use a complete-case approach. Otherwise, multiple imputation will be used. Participants who miss the follow-up will be included and assumed not achieve the primary and secondary outcomes during the missed follow-up period.

We will also carry out a subgroup analysis based on age (> 30 years old versus ≤ 30 years old) and way of HIV testing (facility-based versus self-testing).

In order to measure contamination, we will conduct per protocol sub analyses to measure whether our results have been affected by contamination.

Results of this study will be distributed to target cities and national stakeholders.

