**Methods:**

A two-arm, cluster-randomized controlled trial will be implemented in eleven cities (ten clusters) in Shandong Province, China. Targeted study participants will be 250 MSM per arm and 50 participants per cluster. MSM who are 18 years old or above, live in the study city, have not been tested for HIV in the past 3 months, are not living with HIV or have never been tested for HIV, and are willing to provide informed consent will be enrolled. Participants will be recruited through banner advertisements on Blued, the largest gay dating app in China, and in-person at community-based organizations (CBOs). The intervention includes a series of crowdsourced intervention materials (24 images and four short videos about HIV testing and safe sexual behaviors) and HIV self-test services provided by the study team. The intervention was developed through a series of participatory crowdsourcing contests before this study. The self-test kits will be sent to the participants in the intervention group at the 2nd and 3rd follow-ups. Participants will be followed up quarterly during the 12-month period. The primary outcome will be self-reported HIV testing uptake at 12 months. Secondary outcomes will include changes in condomless sex, self-test efficacy, social network engagement, HIV testing social norms, and testing stigma.

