## Methods

### Design

As the intervention in our study will involve two levels—the community level and the individual level, and MSM in the same city often communicate with each other, we adopt a cluster-randomized controlled trial with one intervention arm and one control arm (Fig. 1). The cluster unit will be the city. Surveys will be conducted at baseline and every 3 months thereafter (Fig. 2). A total of ten clusters, including City A, City B, City C, City D, City E, City F, City G, City H, City I, City J, and City K from Shandong Province, were chosen based on the following criteria: (1) CDC MSM sentinel surveillance sites and (2) capacity for recruiting sufficient MSM. City J and a nearby City K are in the same cluster because the number of estimated MSM in both cities is small.

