### Follow-up

All participants will receive an online survey at baseline and follow-up surveys will be conducted every 3 months. Each man will participate in a total of five surveys. At the 2nd and 3rd follow-ups, we will send self-test kits to the participants in the intervention group to evaluate the effectiveness of self-test kit in improving HIV testing rate.

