### Outcomes

The primary outcome of this study will be the uptake of self-reported HIV testing uptake after 12 months. We have set ten monitoring sentinels in the eleven cities so that the self-reported HIV testing rate can be triangulated with the rate from surveillance data during the same period. In addition, participants who receive the self-test kit are required to send their results to us on WeChat so that we can verify that the self-reported results are consistent with the self-test results. An increase of 20% in testing rate (assuming a proportion of HIV testing of 70% in intervention arm and 50% in control arm) was chosen as the superiority margin. This choice was based on the data of MSM sentinel surveillance collected by CDCs of Shandong Province in last 1 year. Secondary outcomes include condom use, syphilis testing, social network characteristics, and others (see Additional file 4).

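### The primary outcome is set at 12 months, but the model as written gives one intervention effect averaged over months 3, 6, 9 and 12

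*Protocol article*

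**What the plan says.** The outcome is tied to 12 months in three places. The Abstract has "The primary outcome will be self-reported HIV testing uptake at 12 months", the Outcomes section has "The primary outcome of this study will be the uptake of self-reported HIV testing uptake after 12 months", and the Analysis section has "The primary outcome of this trial will be the uptake of self-reported HIV testing rate after 12 months". The Sample size section rests on one pair of rates, 70% and 50%, with no reference to repeated records.

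The Analysis section continues with "Generalized linear mixed models (GLMM) will be used for the analysis" and describes the model: "Intervention status and time will be considered fixed effects, while sites and individual participants with multiple measurements across the four follow-ups" form the random effects. The design section fixes the survey times: "Surveys will be conducted at baseline and every 3 months thereafter". Follow-ups 1 to 4 therefore fall at months 3, 6, 9 and 12.

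The intervention changes partway through. The Follow-up section states: "At the 2nd and 3rd follow-ups, we will send self-test kits to the participants in the intervention group". The data collection section counts self-tests as well as facility tests as HIV testing. The Analysis section also plans an interim look at the images and videos after the 2nd follow-up, and an evaluation of media plus kits from the 3rd and 4th follow-ups.

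**The concern.** The outcome sentence and the model sentence stand side by side but do not describe the same quantity. With intervention and time as the only fixed effects, the time terms shift both arms together. A single intervention coefficient then summarises all four surveys, and nothing in it is specific to month 12.

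This would matter little if the effect were the same in every quarter, but the design makes that unlikely. Follow-ups 1-2 reflect the media alone, and follow-ups 3-4 reflect media plus kits that only one arm receives and whose use counts towards the outcome. The protocol's separate evaluations of the two phases recognise this split.

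At stake is what the confirmatory result means. A 12-month effect could be understated because earlier quarters are averaged in, or an early media effect could be reported as 12-month uptake. While the target stays open, an averaged, a 12-month or a post-kit estimate could each be presented as primary once the data are seen.

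**Working it through.** **1. The plan's own figure.** Inputs from the Sample size section: 70% vs 50%, five clusters per arm, ICC 0.02, two-sided alpha 0.05, power 0.85, 30% loss.

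- Effective men per arm (unpooled variance): (0.70×0.30 + 0.50×0.50) × (1.960 + 1.036)² / 0.20² = 103.3.
- Analysed men per cluster, from 5m / [1 + (m−1)×0.02] = 103.3: m = 103.3×0.98 / (5 − 103.3×0.02) = 34.5, rounded up to 35.
- Enrolled per cluster: 35/0.70 = 50. Total: 10 × 50 = 500.
- Check at m = 35: design effect 1 + 34×0.02 = 1.68; effective n = 175/1.68 = 104.2 per arm; power 0.853 (unpooled) or 0.843 (pooled).

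The stated 500 is reproduced exactly as one comparison of two proportions, one value per man. Repeated measurements play no part in it.

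**2. What the stated model returns.** Assumptions: logit link (the protocol names none); control 50% at every follow-up; intervention 70% at follow-ups 3-4; the same pre-kit effect at follow-ups 1 and 2. The model, with four time effects and one intervention effect, was fitted to these expected probabilities. It was fitted first without random effects, then with a participant random intercept of SD 1 or 2. The site effect was left out.

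| Assumed pre-kit effect (points) | Simple average of four effects | Model odds ratio, no random effects (true at month 12: 2.33) | Model-implied month-12 effect (points; true: 20) | Model log odds ratio / true month-12 log odds ratio, SD 1 / SD 2 |
|---|---|---|---|---|
| 0 | (0+0+20+20)/4 = 10.0 | 1.51 | 9.8 | 0.481 / 0.473 |
| 5 | (5+5+20+20)/4 = 12.5 | 1.67 | 12.3 | 0.605 / 0.600 |
| 10 | (10+10+20+20)/4 = 15.0 | 1.86 | 14.8 | 0.733 / 0.730 |
| 15 | (15+15+20+20)/4 = 17.5 | 2.08 | 17.3 | 0.864 / 0.864 |
| 20 | 20.0 | 2.33 | 20.0 | 1.000 / 1.000 |

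The random-intercept fits give the same month-12 risk differences to within rounding. The model is close to an equal-weight average of the four effects. It matches the 12-month effect only if the full 20 points are present before any kit is sent.

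**3. The other reading of the outcome.** Suppose 70% and 50% mean any test during 12 months. Assuming constant, independent quarterly probabilities:

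- Intervention: 1 − 0.30^(1/4) = 0.260.
- Control: 1 − 0.50^(1/4) = 0.159.
- Difference per quarterly record: 10.1 points, odds ratio 1.86, against 20 points and 2.33 over the year.

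On this reading each man has one outcome value, and a four-record model does not estimate it directly.

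**The case against.** The best defence is that the article lists which factors are fixed and which random and does not say that an interaction is excluded. A model on four follow-ups can deliver a 12-month contrast, and an analysis plan not shown here may name one. That is possible. But the article goes beyond leaving the model open: it specifies one for the primary outcome, and that model followed as written does not target month 12.

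A second defence is the planned evaluation of follow-ups 3 and 4. It lowers the risk of confusing the phases, but it is not named as primary and still pools months 9 and 12.

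Four stronger readings are tempting and are not supported:

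- *The effect cannot be constant.* The components change by design; whether the effect changes is empirical. It is unlikely to be constant, no more.
- *Power is lost.* Four correlated records per man carry more information than one, so a smaller contrast per record does not show lower power. If there is no effect in any quarter, the test still has the right null.
- *The trial was sized on any test within 12 months.* The Sample size section gives a testing rate without defining its window.
- *The result will be on an odds scale.* No link function is stated.

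**Conclusion.** The point holds as a mismatch between the stated outcome and the estimate that the stated model produces. That conclusion needs only the protocol's own sentences, with the fixed effects read as the two named.

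Its size depends on assumptions. With 20 points at follow-ups 3-4 and 0 to 15 points before, the model implies about 10 to 17 points at month 12; with an equal effect throughout there is no discrepancy. The stated power of 0.85 was derived for a single contrast and not for this model, so the power of the model as written is unknown rather than shown to be low.

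**What to change.** First, state whether the 12-month outcome means testing in the last quarter or any test during the 12 months, and apply the same definition to the 70% and 50% in the sample size. Then match the primary analysis to it:

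- **Last quarter:** keep the four-record mixed model, add intervention-by-time, and name the 4th-follow-up contrast as primary.
- **Any test in 12 months:** analyse one record per man with a city random effect, and acknowledge that this outcome spans both the media-only and the media-plus-kit periods.

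In either case keep the average over the four follow-ups as secondary. The change is a few sentences in the Outcomes, Sample size and Analysis sections, with no new data collection. The price is that the 12-month contrast is somewhat less precise than the pooled average.

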### Sample size

A two-arm, cluster-randomized controlled trial will be used. The sample size was calculated based on the primary outcome. We assumed that a digital crowdsourced intervention will be superior to CDC routine intervention in promoting HIV testing rate among MSM who have not been tested in the past 3 months. Assuming the HIV testing rate is 70% in intervention cities and 50% in the control cities, a total of ten clusters (five in intervention group and five in control group), an intraclass correlation coefficient of 0.02 (usually between 0.01 to 0.03), two-sided *α* = 0.05, power = 0.85, and the loss of follow-up is 30%, the total sample size is 500 men (50 for each cluster). The calculation was made using the software PASS 15.

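### Secondary outcomes recorded as counts or scores are to be cut to yes/no before modelling, which gives up precision that the planned mixed model could keep

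*Protocol article*

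**What the plan says.** The second paragraph of the Analysis section describes the secondary outcomes as a set of binary variables and adds in brackets that "continuous variables will be categorized into binary variables". No exception is given. The examples include partner numbers, frequency of anal sex and frequency of HIV testing, next to items such as condomless sex and knowing one's syphilis status. The paragraph then says "These will be analyzed similar with the primary outcomes", which means a GLMM with intervention and time as fixed effects, and site and participant as random effects.

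The Methods part of the Abstract lists the secondary outcomes differently: "Secondary outcomes will include changes in condomless sex, self-test efficacy, social network engagement, HIV testing social norms, and testing stigma". The Analysis section does not name self-efficacy, norms or stigma. They can come under the rule only through its closing reference to other outcomes. The Outcomes section refers the full list to Additional file 4, which is not shown.

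Later in the Analysis section, men who miss a follow-up are counted as not having achieved the primary and secondary outcomes for that period.

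**The concern.** This is a stated analysis choice, so any later analysis plan would inherit it. No reason is given, and the planned model does not require it: a GLMM with the same random effects accommodates counts through a log link and scores through an identity link. Skewness in a count is a reason to use a count model, not a reason to split it in two.

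The second objective in Trial aims, superiority in promoting safer sexual behaviour, rests on these outcomes. The sample size was set for the binary primary outcome alone, so the secondary outcomes have whatever precision ten clusters provide. A split lowers that precision. It also hides graded change: a man who goes from eight partners to four stays in the same category unless the threshold lies between the two. Results then depend partly on where the threshold is placed.

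**Working it through.** **1. The plan's own figure.** The Sample size section gives the inputs: "Assuming the HIV testing rate is 70% in intervention cities and 50% in the control cities", five clusters per arm, intraclass correlation (ICC) 0.02, two-sided alpha 0.05, power 0.85 and 30% loss.

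- Effective number per arm, unpooled variance: (1.960 + 1.036)² × (0.7×0.3 + 0.5×0.5) / 0.2² = 8.978 × 0.46 / 0.04 = 103.3.
- Solve 5m / [1 + (m − 1)×0.02] = 103.3. This gives m = 34.5, so 35 completers per cluster.
- 35 / 0.70 = 50 enrolled per cluster, and 10 × 50 = 500.

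The stated 500 is reproduced. It concerns an outcome that is binary by nature and does not depend on the rule discussed here. The figures carried forward are m = 35 and ICC = 0.02. The article gives no figure for information lost by splitting, and no distribution or cut-point for any secondary outcome. Everything below therefore rests on stated assumptions.

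**2. Independent normal data (assumption).** Efficiency of a split leaving proportion p on one side is φ(z_p)² / [p(1 − p)], where φ is the standard normal density.

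| Split | Efficiency | Loss |
|---|---|---|
| 50/50 | 0.637 | 36% |
| 30/70 | 0.576 | 42% |
| 20/80 | 0.490 | 51% |
| 10/90 | 0.342 | 66% |

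**3. Allowing for the clustering.** Splitting also lowers the ICC, so part of the loss is recovered through a smaller design effect. Efficiency becomes the value above × [1 + (m − 1)·ICC_cont] / [1 + (m − 1)·ICC_bin]. ICC_cont is taken as 0.02, and ICC_bin is derived from the bivariate normal. The numerator is 1 + 34×0.02 = 1.68.

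- Median split: ICC_bin = 0.0127, design effect 1.43, efficiency 0.637 × 1.68 / 1.43 = 0.75. Loss about 25%.
- 20/80 split: ICC_bin = 0.0099, design effect 1.34, efficiency 0.490 × 1.68 / 1.34 = 0.62. Loss about 38%.
- By the same steps, about 31% at 30/70 and 53% at 10/90.
- Over the article's ICC range of 0.01 to 0.03, the loss runs from 30% to 22% at the median and from 44% to 34% at 20/80.
- If all 50 men per cluster were analysed, the numerator would be 1 + 49×0.02 = 1.98 and the denominators 1.62 and 1.49. The losses would be about 22% and 35%.

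**4. Effect on power.** Take an outcome with 80% power on its own scale. After the split, power = Φ[(1.960 + 0.842)×√efficiency − 1.960].

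- Median: 2.802 × √0.746 − 1.960 = 0.46, power about 68%.
- 20/80: 2.802 × √0.616 − 1.960 = 0.24, power just under 60%.

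**5. Counts.** Here efficiency = (dP/dμ)² × V / [P(1 − P)]. P is the probability of reaching the cut, and V = μ for a Poisson count or μ + μ²/k for a negative binomial count with known dispersion k. This is for independent data, with illustrative means.

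- Poisson, mean 0.5, any versus none: 0.771 (loss 23%).
- Poisson, mean 2, three or more: 0.670 (loss 33%).
- Negative binomial, k = 1, mean 2, three or more: 0.632 (loss 37%).
- Negative binomial, k = 1, mean 2, any versus none: 0.333 (loss 67%).

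Among the cases examined, the smallest loss is about a quarter. A badly placed cut loses well over half.

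These calculations use one time point and large-sample formulas. With ten clusters they are indicative.

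**The case against.** A reader might infer that the rule throws away a third to a half of the information on every secondary outcome. The documents do not support that. The range belongs to independent normal data split between 50/50 and 20/80. With the trial's clustering the same splits lose about 25% to 38%, and the outcomes that the Analysis section names are largely counts, to which the normal formula does not apply. Some listed items, such as condomless sex and knowing one's syphilis status, may be binary as collected and then lose nothing. That the scores come under the rule is an inference. The Abstract's reference to changes does not prove a continuous scale, since condomless sex is in the same list. Response formats may be in Additional file 1, so a frequency collected only in bands could not be modelled as a count. The lack of cut-points in a journal article is no finding.

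Nor can the number analysed simply be taken as 350, which is 500 less the 30% planning loss. The Analysis section keeps men who miss follow-up by assuming non-achievement, so 35 per cluster is a planning figure.

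The best point on the other side is practical. The binary form gives an effect that is easy to quote, and it is what makes the non-achievement rule for missed follow-ups workable. A count or score has no equivalent of not achieved. That stands, and the change has to deal with it. It does not justify the split as the main analysis, because the same section already provides for multiple imputation.

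**Conclusion.** The point holds for secondary outcomes recorded as counts or scores. Splitting them is a stated, unexplained choice that costs precision on the second aim. Under assumed normality, ICC 0.02 and 35 completers per cluster, the cost is about 25% of the information at a median split and 38% at 20/80. For counts the size cannot be fixed without the mean, the dispersion and the cut. The direction and the existence of a material loss are secure; the exact size is not.

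The primary outcome, its sample size and any outcome that is already binary are untouched. It would also go too far to say that the secondary outcomes are underpowered: the article states no target effect for them. This is a cheap improvement.

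**What to change.** In the Analysis section, replace the general rule with one that follows how each outcome is recorded:

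- **Counts:** negative binomial mixed model.
- **Scores:** linear mixed model adjusted for the baseline value.
- **Outcomes collected only in bands:** ordinal mixed model.
- **Outcomes binary as collected:** as now planned.

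Use the same site and participant random effects throughout. Keep the binary version of each count or score as a supportive summary.

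For counts, scores and banded outcomes, handle missed follow-ups by likelihood-based analysis or by the plan's multiple imputation. Limit the assumption of non-achievement to binary outcomes.

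The cost is some wording in the analysis plan, a model-fit check for the skewed counts, and effect measures (rate ratios, mean differences) that are less simple to quote than a difference in proportions. No new data or participants are needed.

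### Two conflicting rules cover men who miss a follow-up survey; at the planned 30% loss they target 20 or 14 points, and only one of them fits the sample size

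*Protocol article*

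**What the plan says.** The Analysis section of the protocol article gives two instructions in adjacent sentences. The first depends on how much is missing: "If an outcome is missing for < 15% of participants, analyses will use a complete-case approach. Otherwise, multiple imputation will be used". The second depends on attendance: "Participants who miss the follow-up will be included and assumed not achieve the primary and secondary outcomes during the missed follow-up period". Nothing restricts either rule to one kind of missing data, and neither is called primary or sensitivity. The second names the primary outcome expressly.

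Two other places bear on how these fit together. Data collection and management says: "All questions in our online survey have been set as compulsory questions, which can improve data completeness". Sample size plans for heavy loss: "the loss of follow-up is 30%, the total sample size is 500 men (50 for each cluster").

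**The concern.** A man who misses the 12-month survey cannot be both imputed and set to not tested. If missed surveys are set to failure, almost nothing is left to delete or impute. If the threshold rule governs, the failure rule is never used. The text does not say which sentence to follow, and the primary risk difference, the odds ratio and the power all depend on it.

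The failure rule is also not safely conservative for a comparison between arms. It multiplies each arm's testing rate by that arm's retention, so a difference in survey completion appears as a difference in HIV testing. Retention could plausibly differ. Under Intervention, one arm receives material on WeChat every 2 weeks, discussion groups and self-test kits, and the other receives the routine local CDC intervention.

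**Working it through.** **Inputs.** Testing rates come from Sample size: "Assuming the HIV testing rate is 70% in intervention cities and 50% in the control cities". The same 20-point difference is given under Outcomes. Sample size also gives "a total of ten clusters (five in intervention group and five in control group") and "an intraclass correlation coefficient of 0.02 (usually between 0.01 to 0.03"), with two-sided α = 0.05, power 0.85 and 30% loss. Retention by arm is not given, so the unequal splits in step 5 are assumptions.

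**1. Reproduce the 500.** For two proportions with unpooled variance, the effective number per arm is

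n = [0.7×0.3 + 0.5×0.5] × (1.960 + 1.036)² / 0.20² = 103.25.

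With K = 5 clusters per arm and ICC 0.02, the completers needed per cluster are

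m = n(1 − ICC)/(K − n×ICC) = 103.25×0.98/(5 − 2.065) = 34.5, rounded up to 35.

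Then 35/(1 − 0.30) = 50 per cluster, or 500 in total, an exact match. A pooled variance gives 530 and a continuity correction 620. So the plan's figure comes from analysing 35 completers of 50 per cluster, with lost men out of the calculation.

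**2. Target under each rule.** Assume equal 30% loss, loss unrelated to testing, and the outcome read at the 12-month survey.

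| | Intervention | Control | Difference | Odds ratio | Risk ratio |
|---|---|---|---|---|---|
| Multiple imputation (or complete case) | 70% | 50% | 20 points | 2.33 | 1.40 |
| Missed = not tested | 0.7×70% = 49% | 0.7×50% = 35% | 14 points | 1.78 | 1.40 |

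**3. Power under each rule at ICC 0.02** (normal approximation, as in step 1).
- Threshold rule, 35 per cluster: effective n = 175/(1 + 34×0.02) = 104.2; SE = √(0.46/104.2) = 0.0665; 0.20/0.0665 − 1.960 = 1.05; power 85%.
- Missed = not tested, all 50 per cluster: effective n = 250/(1 + 49×0.02) = 126.3; SE = √[(0.49×0.51 + 0.35×0.65)/126.3] = 0.0615; 0.14/0.0615 − 1.960 = 0.32; power 62%.
- Over the plan's ICC range, the second figure is 75% at 0.01 and 53% at 0.03.

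**4. Below the threshold.** At 14% equal loss, where complete case would apply, the targets are 20 points and 0.86×20 = 17.2 points. The conflict is smaller but does not disappear.

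**5. Unequal retention under missed = not tested, no true effect (50% testing in both arms).**
- Retention 75% vs 65%: 37.5% vs 32.5%, a spurious 5 points.
- Retention 80% vs 60%: 40% vs 30%, a spurious 10 points.

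**The case against.** The best defence is that the two sentences cover different gaps: missed surveys count as failures, and other missing outcomes follow the threshold. That reading is not impossible. Compulsory questions are said only to help completeness, a single logical error is queried with the participant and might stay unresolved, and the questionnaire itself is in an additional file that is not shown. But the article does not state this division. More than one logical error removes the man from the study, so what remains for the threshold rule would be a small residue. The overlap is therefore near-complete in practice, though not proven to be total.

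Several stronger readings are tempting and are not supported:

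- A reader might count three incompatible rules. Complete case and multiple imputation are two branches of one rule, split at 15%, and do not clash with each other.
- A reader might say that the branch below 15% contradicts the 30% planned loss. A contingency branch does not contradict a cautious planning figure, and the imputation branch covers 30%.
- A reader might take 20 vs 14 as following from the trial's assumptions alone. It also needs equal, non-informative loss and an outcome read at month 12. If the outcome is any test over the four follow-ups, a man who misses one survey can still count as tested, and the gap is smaller.
- A reader might attach false-positive rates to the unequal-retention cases. At ICC 0.02 a normal test rejects in about 13% (75 vs 65) and 39% (80 vs 60) of trials, but with five clusters per arm a t reference on 8 degrees of freedom gives about 11% and 31%. Both rest on assumed splits. Shared measures also work against a large split: both arms join the study's WeChat contact, are paid for each survey and can enter the prize draw.
- A reader might fear a choice of rule steered by the result. The analysts are to be blinded to allocation, which limits that. Blinding still does not tell them which sentence to follow.

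Labelling a sensitivity analysis can be left to an analysis plan. Two stated rules that give different primary results cannot.

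**Conclusion.** The conflict stands as a two-way one: the threshold rule against missed = not tested. At the planned 30% loss it is multiple imputation against failure. Under the assumptions in step 2, the choice moves the target from 20 to 14 points and the odds ratio from 2.33 to 1.78, and leaves the risk ratio at 1.40. Power falls from the stated 85% to about 62% at ICC 0.02. The sample size agrees with the threshold rule and not with the failure rule.

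The distortion from unequal retention in step 5 arises under missed = not tested. Its size is illustrative, because the article gives no retention by arm. It should not be read as a claim that retention will differ or that any unequal retention biases the trial whichever rule is used.

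**What to change.** State one primary rule for missed surveys that is consistent with the Sample size section. Either fit the mixed model to all observed follow-ups, or use multiple imputation by arm that accounts for city. Move missed follow-up = not tested to a named sensitivity analysis, reported with retention by arm. If missed = not tested is kept as the primary rule, restate the power in Sample size.

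The cost is one reworded paragraph and one labelled sensitivity analysis, with no change to data collection. The downside is that the main estimate then relies on a missing-at-random assumption, which the sensitivity analysis probes.
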